### Intervention

Participants that are randomized to the HLST group will take part in a 12-week, supervised exercise program at a frequency of 2 days per week. The HLST group will progress to lifting heavy loads (80% to 100% of maximal perceived exertion) of low repetitions (i.e., 1–6) for the barbell squat, bench press, and deadlift. If they are not able to safely execute the prespecified strength movements after multiple attempts, the following substitutions were planned for the duration of the 12-week intervention: leg press to replace the barbell squat, dumbbell bench press to replace the barbell bench press, rack pulls or dumbbell deadlifts to replace the barbell deadlift from the floor. Accessory exercises, which target smaller muscles, will also be included in the exercise protocol and include: face pulls, seated rows, dumbbell lunges, farmers carry, and planks. The planned intensity progression of the three primary exercises in the LIFTING 2 trial are presented in **Fig 2**.

**Fig 2 pone.0326860.g002:**
[figure not shown]
Planned intensity progressions in the LIFTING 2 trial. %1RM: percent of one-repetition maximum.

Details of the exercise intensity progression phases are as follows:

In weeks 1–2, the weight is chosen based on warmup sets that would only allow for 10 repetitions (10RM), which is approximately equivalent to 70% to 75% 1RM. In weeks 3–5, the weight is chosen based on warmup sets and previous sessions that would only allow for 8 repetitions (8RM), which is approximately equivalent to 75% to 80% 1RM. In weeks 6–8, the weight is chosen based on warmup sets and previous sessions that would only allow for 5 repetitions (5RM), which is approximately equivalent to 80% to 85% 1RM. In weeks 9–12, the weight is chosen based on warmup sets and previous sessions that would only allow for 1–3 repetitions (≤ 3RM), which is approximately equivalent to 90% to 100% 1RM.

Prior to exercise testing and each exercise session, resting heart rate and resting blood pressure values will be assessed. Additionally, participants will be asked to rate their current level of perceived fatigue and pain, on a scale of 0 (no fatigue/pain) to 10 (worst possible fatigue/pain). All participants in the HLST group will be guided through a 10-minute warm up. This will consist of low intensity biking or walking on the treadmill for 5 minutes, and structured dynamic movements such as leg swings, arm circles, hip, shoulder, and ankle mobility exercises. At the end of each session, all participants will be guided through a 10-minute cool down. This will consist of structured static stretching. Exercise intensity will be gradually progressed over a period of at least 5-weeks to reach heavy loads (80% to 100% of maximal perceived exertion) for the barbell squat, bench press, and deadlift (**Table 2**).

**Table 2 pone.0326860.t002:** The 12-week, heavy lifting strength training periodization scheme in the LIFTING 2 trial. 1RM: one repetition maximum.

Week	1		2		3		4		5		6		7		8		9		10		11		12	
**Exercise Sessions**	1	2	3	4	5	6	7	8	9	10	11	12	13	14	15	16	17	18	19	20	21	22	23	24
**Repetitions**	**10**		**10**		**8**		**8**		**8**		**5**		**5**		**5**		**1-3**		**1-3**		**1-3**		**1-3**	
**1RM Equivalency (%)**	**70-75% 1RM**		**70-75% 1RM**		**75-80% 1RM**		**75-80% 1RM**		**75-80% 1RM**		**80-85% 1RM**		**80-85% 1RM**		**80-85% 1RM**		**90-100% 1RM**		**90-100% 1RM**		**90-100% 1RM**		**90-100% 1RM**	

Participants that are randomized to the UC group will be asked to continue with their typical daily routine and habit of exercise during the 12-week intervention period. They will not receive any information or education regarding exercise. After the post-intervention assessments at 12-weeks, the UC group will be offered a 4-week introduction to HLST program and/or referred to a community-based exercise program.

### Feasibility and safety measures

The feasibility and safety outcomes will be determined based on the interest rate (number of HNCS who contact us), eligibility rate (with reasons for ineligibility), recruitment rate (with reasons for refusal), 3RM testing rate (with reasons for not completing the test), HLST program adherence (including attendance, dose modifications, and progression), follow-up assessment rate (with reasons for drop out), and adverse events.

The following thresholds have been adopted as indicating issues with feasibility requiring protocol modification prior to further efficacy testing: 1) Safety Concerns: > 10% of participants in the HLST group report injuries and/or adverse events likely related to the exercise intervention, which will be reported to our ethics board and the Principal Investigator ([name]) immediately; 2) Recruitment: failure to recruit 48 patients from Edmonton, Alberta which may indicate the need for a multi-centre trial moving forward; 3) Attrition Rate: > 20% of randomized participants drop out of the study; or 4) Adherence: 80% of participants adhere to the protocol.

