### Outcomes

Participant characteristics, behavioural outcomes, feasibility outcomes, health-related fitness and patient-reported outcomes, physical function, anthropometry and body composition will be assessed in this study. The instruments that will be used and the timepoints of assessments are shown in **Table 3**.

**Table 3 pone.0326860.t003:** Outcome measures and assessment timepoints of the LIFTING 2 trial.

PARTICIPANT CHARACTERISTICS	INSTRUMENT	BASELINE	POST-INTERVENTION (3 months)
Demographic Variables	Self-Report	X	
Medical Information	Self-Report	X	
**BEHAVIOURAL OUTCOMES**	**INSTRUMENT**	**BASELINE**	**POST-INTERVENTION** **(3 months)**
Social Cognitive Behaviours (i.e., motivation)	Questions informed by the Theory of Planned Behaviour	X	X
Alcohol Consumption	Self-Report	X	
Smoking Status	Self-Report	X	
Exercise Levels	Godin Leisure Time Exercise Questionnaire (Self-Report)	X	X
**FEASBILITY OUTCOMES**	**INSTRUMENT**	**ASSESSED ON AN ONGOING BASIS**	
Interest Rate	# (%) HNCS who contact us	X	
Eligibility Rate	# (%) HNCS eligible and ineligible with reasons for ineligibility	X	
Recruitment Rate	# (%) HNCS randomized with reasons for refusal	X	
3RM Testing Rate HLST Program Adherence	# (%) of exercise sessions completed including attendance, dose modifications, and progression	X	
		**BASELINE**	**POST-INTERVENTION** **(3 months)**
Follow-Up Assessment Rate	# (%) HNCS who completed post-intervention physical assessments and questionnaires with reasons for dropout		X
Adverse Events	# (%) injuries and/or undesired effects related to exercise intervention		X
**HEALTH-RELATED FITNESS OUTCOMES**	**INSTRUMENT**	**BASLEINE**	**POST-INTERVENTION** **(3 months)**
Muscular Strength			
Lower Body Strength	3RM leg press	X	X
Upper Body Strength	3RM chest press	X	X
**PATIENT-REPORTED OUTCOMES**	**INSTRUMENT**	**BASELINE**	**POST-INTERVENTION** **(3 months)**
Quality of Life	EORTC QLQ-C30	X	X
Fear of Cancer Recurrence	Fear of Cancer Recurrence Inventory	X	X
Head & Neck Cancer Symptom Burden	Neck Dissection Impairment Index	X	X
Self-Esteem	Rosenberg Self-Esteem Scale	X	X
Sleep Quality	Insomnia Severity Index	X	X
Swallowing Abilities	MD Anderson Dysphagia Inventory	X	X
**PHYSICAL FUNCTION**	**INSTRUMENT**	**BASELINE**	**POST-INTERVENTION** **(3 MONTHS)**
Aerobic Functional Capacity	6 Minute Walk Test	X	X
Lower Body Muscular Endurance	30 Second Sit to Stand	X	X
Shoulder Ranges of Motion	Active Flexion	X	X
	Active Abduction	X	X

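### The adherence threshold (item 4) is worded in the wrong direction: as written, reaching 80% adherence counts as a feasibility problem

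*Protocol article*

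**What the plan says.** The primary aim is feasibility of HLST (Abstract, Background). Feasibility and safety measures then sets the decision thresholds. The lead-in is: "The following thresholds have been adopted as indicating issues with feasibility requiring protocol modification prior to further efficacy testing". Four items follow, joined by 'or':

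1. Safety: "> 10% of participants in the HLST group report injuries and/or adverse events likely related to the exercise intervention".
2. Recruitment: "failure to recruit 48 patients from Edmonton, Alberta".
3. Attrition: "> 20% of randomized participants drop out of the study".
4. "4) Adherence: 80% of participants adhere to the protocol".

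The paragraph before the list names the outcome as "HLST program adherence (including attendance, dose modifications, and progression" (a parenthesis that closes there). Table 3, under Outcomes, gives its instrument as the number and percentage "of exercise sessions completed including attendance, dose modifications, and progression". The later subsection on feasibility and safety outcomes repeats the outcome list but no threshold.

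**The concern.** Whatever meets an item on this list is, by the lead-in, a reason to change the protocol before going further. Items 1 to 3 fit that sense. Item 4 does not: it names a level of adherence that most investigators would be glad to reach, and it has no inequality sign and no word such as 'fewer'.

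These thresholds are the prespecified decision rule for the trial's primary aim, and the Discussion makes planning of a phase III trial depend on feasibility being established. Because the items are joined by 'or', one reversed item is enough to flag a programme that succeeded on all four counts. If the wording is repaired only after adherence is known, the repair can be challenged as post hoc, however obvious it was.

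**Working it through.** **Text check.** The items side by side:

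| Item | Condition listed as a problem | Direction |
|---|---|---|
| 1 Safety | more than 10% of HLST participants with related events | failure |
| 2 Recruitment | fewer than 48 recruited | failure |
| 3 Attrition | more than 20% drop out | failure |
| 4 Adherence | 80% adhere | success |

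A symbol lost when the text was extracted is unlikely. The 'greater than' signs survive in the same sentence, and 'less than' signs survive in Sample size and Statistical considerations.

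**Inputs.** The 80% threshold has no derivation in the article, so there is no stated figure for it to reproduce. The sample size behind the denominator does reproduce: 2 × (1.960 + 0.842)² × (1 − 0.25) / 0.80² = 18.4, rounded up to 19 per group, so 38 evaluable; 38 / (1 − 0.20) = 47.5, rounded up to 48. With 1:1 allocation (Randomization and blinding), 48 / 2 = 24 in HLST.

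**Exactly 80%.** 0.80 × 24 = 19.2 and 0.80 × 48 = 38.4. Neither is a whole number, so a rule meaning exactly 80% could never be met at full recruitment.

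**At least 80%.** With 24 participants the cut is 20 (20/24 = 83.3%). Let X be the number adherent, binomial with n = 24 and true adherence p.

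- Literal rule flags a problem: P(X ≥ 20) = Σ C(24,k) pᵏ (1 − p)²⁴⁻ᵏ, k = 20 to 24.
- Corrected rule flags a problem: P(X ≤ 19) = 1 − P(X ≥ 20).

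| True adherence p | Literal rule flags | Corrected rule flags |
|---|---|---|
| 60% | 0.013 | 0.987 |
| 70% | 0.111 | 0.889 |
| 80% | 0.460 | 0.540 |
| 90% | 0.915 | 0.085 |
| 95% | 0.994 | 0.006 |

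The columns are exact complements. If all 48 are the denominator (cut 39), the figures at 90% are 0.981 and 0.019.

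**Participants versus sessions.** Item 4 counts participants; Table 3 counts sessions. Table 2 gives 24 sessions each, so 24 × 24 = 576 in all. Purely for illustration, call a participant adherent at 80% or more of sessions.

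- 18 attend all 24 and 6 attend 12: sessions (432 + 72) / 576 = 87.5%; participants 18/24 = 75%.
- 20 attend 20 and 4 attend 12: sessions (400 + 48) / 576 = 77.8%; participants 20/24 = 83.3%.

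The two summaries can fall on opposite sides of 80%.

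**The case against.** The strongest reply is that nobody would apply item 4 literally. The lead-in and the other three items make the intended direction plain, and the Discussion calls the earlier pilot's 95.8% median attendance excellent. This stands as far as it goes. A reader might infer that the feasibility question will be decided wrongly; the article supports only that it would be if the rule were applied as written. A failing programme could also still be caught by items 1 to 3. But a prespecified rule should not depend on its readers correcting it.

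A reader might also infer that the wrong adherence measure is being collected. That does not follow. A count of adherent participants can be derived from session records, and a journal article may leave the per-participant cut to a fuller document. The denominator is most naturally the HLST group, since the outcome is named as HLST adherence. Some ambiguity remains because Statistical considerations also speaks of protocol adherence in the usual-care group. These are points to settle while correcting item 4, not separate errors.

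Finally, a reader might infer that item 3 is flawed too, because it pools both arms: 9 dropouts of 48 (18.75%) raise no flag, although all nine in HLST would be 9/24 = 37.5%. The documents do not support calling this an error. The rule is clear, it agrees with the 20% loss allowed in Sample size, and retention in usual care matters for a future two-arm trial. Follow-up is to be reported with reasons for dropout. An HLST-only rule would ignore usual-care losses and, at 15% true dropout in both arms, would raise the false-flag probability from 0.17 to 0.29. Pooling is a defensible choice.

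**Conclusion.** Item 4 is wrong as written, and this rests on the article's text alone: it contradicts its own lead-in and the direction of its three companions, and no other section corrects it. Taken literally it either reverses the adherence decision or, if read as exactly 80%, can never be met at full recruitment. The probabilities assume 24 HLST participants who adhere independently with a common probability; the reversal itself needs neither assumption. The practical risk is limited because the intent is easy to guess and adherence is one of four criteria. No treatment-effect estimate or test is affected.

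**What to change.** Reword item 4 along these lines: *Adherence: fewer than 80% of participants allocated to HLST are adherent.* This brings it into line with the lead-in, items 1 to 3 and the named adherence outcome, and it settles the denominator.

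As a secondary step in the same edit, state what share of the Table 3 sessions makes a participant adherent, and whether dose modifications and progression count towards it, or point to the document that says so. Item 3 needs no change.

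The cost is a wording amendment. No new data, participants or analyses are needed. It should be dated before the adherence results are summarised.

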### Prespecified criteria for stopping or changing the study protocol due to safety concerns

A participant may be discontinued at any time if the participant, the investigator, or the primary physician feels that it is not in the patient’s best interest to participate in the study, the physical assessments, and/or questionnaires. This includes any adverse events (related or unrelated to the study intervention) that cannot be ameliorated by the use of adequate medical intervention, exercise intervention modifications, or would lead to undue risk if the participant were to continue with the study procedures.

A resting heart rate ≥100 bpm, resting blood pressure ≥160/90 mmHg will result in no exercise testing or exercise sessions to be conducted for safety reasons. An injury related or unrelated to the exercise intervention will result in program modifications including reducing the load, sets, and/or repetitions, or completely removing an exercise if necessary, depending on the severity of the injury. Exercise intensity will gradually progress overtime. However, volume will be modified or remain unchanged if participants are unable to safely progress. During 3RM testing and exercise sessions, technique and perceived pain will regularly be monitored.

### Outcomes

Participant characteristics, behavioural outcomes, feasibility outcomes, health-related fitness and patient-reported outcomes, physical function, anthropometry and body composition will be assessed in this study. The instruments that will be used and the timepoints of assessments are shown in **Table 3**.

**Table 3 pone.0326860.t003:** Outcome measures and assessment timepoints of the LIFTING 2 trial.

PARTICIPANT CHARACTERISTICS	INSTRUMENT	BASELINE	POST-INTERVENTION (3 months)
Demographic Variables	Self-Report	X	
Medical Information	Self-Report	X	
**BEHAVIOURAL OUTCOMES**	**INSTRUMENT**	**BASELINE**	**POST-INTERVENTION** **(3 months)**
Social Cognitive Behaviours (i.e., motivation)	Questions informed by the Theory of Planned Behaviour	X	X
Alcohol Consumption	Self-Report	X	
Smoking Status	Self-Report	X	
Exercise Levels	Godin Leisure Time Exercise Questionnaire (Self-Report)	X	X
**FEASBILITY OUTCOMES**	**INSTRUMENT**	**ASSESSED ON AN ONGOING BASIS**	
Interest Rate	# (%) HNCS who contact us	X	
Eligibility Rate	# (%) HNCS eligible and ineligible with reasons for ineligibility	X	
Recruitment Rate	# (%) HNCS randomized with reasons for refusal	X	
3RM Testing Rate HLST Program Adherence	# (%) of exercise sessions completed including attendance, dose modifications, and progression	X	
		**BASELINE**	**POST-INTERVENTION** **(3 months)**
Follow-Up Assessment Rate	# (%) HNCS who completed post-intervention physical assessments and questionnaires with reasons for dropout		X
Adverse Events	# (%) injuries and/or undesired effects related to exercise intervention		X
**HEALTH-RELATED FITNESS OUTCOMES**	**INSTRUMENT**	**BASLEINE**	**POST-INTERVENTION** **(3 months)**
Muscular Strength			
Lower Body Strength	3RM leg press	X	X
Upper Body Strength	3RM chest press	X	X
**PATIENT-REPORTED OUTCOMES**	**INSTRUMENT**	**BASELINE**	**POST-INTERVENTION** **(3 months)**
Quality of Life	EORTC QLQ-C30	X	X
Fear of Cancer Recurrence	Fear of Cancer Recurrence Inventory	X	X
Head & Neck Cancer Symptom Burden	Neck Dissection Impairment Index	X	X
Self-Esteem	Rosenberg Self-Esteem Scale	X	X
Sleep Quality	Insomnia Severity Index	X	X
Swallowing Abilities	MD Anderson Dysphagia Inventory	X	X
**PHYSICAL FUNCTION**	**INSTRUMENT**	**BASELINE**	**POST-INTERVENTION** **(3 MONTHS)**
Aerobic Functional Capacity	6 Minute Walk Test	X	X
Lower Body Muscular Endurance	30 Second Sit to Stand	X	X
Shoulder Ranges of Motion	Active Flexion	X	X
	Active Abduction	X	X
Handgrip Strength	Handgrip dynamometer (Jamar)	X	X
**ANTHROPOMETRY AND BODY COMPOSITION**	**INSTRUMENT**	**BASELINE**	**POST-INTERVENTION** **(3 MONTHS)**
Fat Mass	Bioelectrical Impedance Analysis (InBody 770)	X	X
Lean Compartments			
Phase Angle			
Height	Stadiometer	X	X
Weight	Beam Scale	X	X
Body Mass Index	Weight (kg)/Height (m^2^)	X	X
Waist to Hip Ratio	Measuring tape	X	X
Nutritional Status	GLIM and PG-SGA	X	X

3RM: 3 repetition maximum; EORTC QLQ-C30: European Organization for Research and Treatment Quality of Life Questionnaire Core 30-item; GLIM: Global Leadership Initiative on Malnutrition; PG-SGA: Scored Patient Generated Subjective Global Assessment

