### Maximal strength testing

Two separate 3RM tests will be used for baseline and post-intervention physical assessments to evaluate upper and lower body strength with the leg press and chest press machines. Maximal testing is safe, reliable, and the gold standard for assessing muscle strength in healthy, older adults [31]. Prior to attempting these movements, the study coordinator will give an in-depth explanation of the purpose of the tests, how to safely execute the lifts, and a demonstration.

To begin, after a 5-minute aerobic warm up and standardized dynamic stretches, study participants will perform bodyweight and resistance band movements to practice appropriate technique. Progressions leading up to the 3RM are as follows. For the leg press, participants will initially perform 8–10 reps at less than 50% of body weight in pounds. To follow, the reps will decrease as the weight gradually increases based on body weight in pounds: 50% body weight for 5–6 reps, 70% for 2–3 reps, and 85%, 90%, 95%, and 100%+ for 3 repetitions. For the chest press, after warming up with a resistance band, participants will perform 8–10 reps at less than 35% of body weight in pounds. Following this, the reps will also decrease as the weight gradually increases based on body weight in pounds: 35% body weight for 5–6 reps, and 40%+ for 3 reps. 3RM tests will be performed in this order: leg press, followed by chest press.

In order to assess a true 3RM, the following factors will be considered. Since the Borg RPE Scales are primarily used to assess intensity of aerobic exercise and may be inaccurate and difficult to conceptualize for beginner lifters [32], a repetition in reserve (RIR)-based RPE scale will be used to assess exercise intensity, which may be more valid to assess maximal or near maximal strength than RPE alone [32]. After each set during the physical assessments, participants will be asked for their RPE, which corresponded to a number on the RIR scale. Participants will be asked the following question, “If I didn’t stop you, how many more repetitions could you have done after the prescribed number?” Conversions from RPE to RIR are as follows: RPE 10 = RIR 0 (maximum effort), RPE 9 = RIR 1, RPE 8 = RIR 2…RPE 1 = RIR 9+ (little to no effort) (44). For maximal testing, participants should report an RIR of 0–1, or RPE of 9–10, in order for the lift to be considered a true maximal test.

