### Statistical considerations

All randomized participants will be included in the analysis using an intention-to-treat approach. There will be no interim analyses. If missing data is < 10% we will conduct a complete case analysis. If missing data is > 10%, we will employ a multiple imputation missing data strategy [54,55]. Continuous variables will be described using mean (standard deviation) or median (interquartile range). Categorical variables will be described using frequencies (percentages) and confidence intervals. Descriptive analyses will be performed for participant characteristics, feasibility outcomes, adherence, and adverse events. Analysis of covariance will be performed to compare post-intervention between-group differences post-intervention in health-related fitness and patient-reported outcomes for patients with evaluable data. We will adjust for covariates such as baseline physical function levels, cancer stage, HPV status, treatments received (surgery, chemotherapy/radiotherapy, surgery + chemoradiotherapy), and time since treatment completion in the primary analysis. IBM SPSS Statistics version 28 will be used for all statistical analyses. The level of statistical significance will be set at 0.05, and all hypotheses’ tests will be two-sided.

Strategies to minimize dropouts and protocol deviations include: 1) a progression period of at least 5-weeks is in place to reach heavy loads (80% to 100% of maximal perceived exertion) in the barbell squat, bench press, and deadlift; 2) reducing the load, number of sets, and/or repetitions; 3) allowing for multiple rest days in between the two weekly exercise sessions; and 4) participants in the Usual Care Group will be offered a 4-week introduction to HLST program and/or referred to a community-based exercise program to encourage their adherence to the protocol, and to thank them for their time in the study. All participants who withdraw from the study will be invited to complete the follow-up assessments to avoid missing data for the intention-to-treat analyses.

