
The LIFTING 2 trial has several strengths including the understudied patient population of HNCS, the randomized controlled trial design with a non-exercise comparison group, the HLST supervised exercise sessions, the free weight HLST intervention, the validated measurement tools and questionnaires used, and the list of comprehensive outcomes that will be assessed. To our knowledge, the LIFTING 2 trial is the first randomized controlled trial to test the feasibility and safety of a HLST program in HNCS. The study will further establish the feasibility of HLST in HNCS by reporting adherence rates, recruitment rates, retention rates, and adverse events related to the exercise intervention. In addition, the LIFTING 2 trial will also provide preliminary evidence on whether exercise may improve health-related fitness and patient-reported outcomes in HNCS at least one-year post-treatment. This study may inform larger phase II and III trials designed to test the efficacy of strength training on important clinical outcomes including muscle strength, mass, and function, symptom management, and QoL.

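### Table 3 counts adverse events only if related to the exercise intervention, so an injury from a completed 3RM test need not be counted

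*Protocol article*

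**What the plan says.** The only place in the protocol article that states how adverse events are measured is Table 3 (Methods, Outcomes). The row gives the number and percentage of "injuries and/or undesired effects related to exercise intervention". The baseline cell is empty and only the post-intervention cell is marked. The closing paragraph of the Discussion describes the planned report in the same terms: "reporting adherence rates, recruitment rates, retention rates, and adverse events related to the exercise intervention".

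Elsewhere the outcome is named without that limit. Feasibility and safety measures, and the matching paragraph under Outcomes, simply list adverse events. Statistical considerations says: "Descriptive analyses will be performed for participant characteristics, feasibility outcomes, adherence, and adverse events". None of these places gives a measure.

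On the tests, Maximal strength testing says: "Two separate 3RM tests will be used for baseline and post-intervention physical assessments". Under Randomization and blinding, allocation follows the baseline assessments. The usual-care group receives no exercise information or education during the 12 weeks, but Table 3 schedules the leg press and chest press tests for everyone at both visits.

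**The concern.** The primary aim is feasibility, safety is assessed alongside it, and maximal strength testing is part of what is being tried out: the 3RM testing rate is itself a listed feasibility outcome. The article's stated safety support for maximal testing concerns healthy older adults. The participants here are head and neck cancer survivors at least one year after treatment who have not recently met the strength-training guideline.

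If the count covers only events related to the intervention, harm from the tests can fall outside it. A later trial that reuses the tests would then inherit a completion rate, but no stated count of injuries from the tests that were completed.

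**Working it through.** The plan gives no figure on this point, so the check sets the relevant places side by side.

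**1. Does the article treat testing as part of the intervention?** Its wording keeps the two apart.
- Methods, Intervention: "Prior to exercise testing and each exercise session, resting heart rate and resting blood pressure values will be assessed". Testing and sessions are named as two activities.
- Prespecified criteria for stopping or changing the study protocol: a raised resting heart rate or blood pressure "will result in no exercise testing or exercise sessions to be conducted for safety reasons". The same pair appears again.
- Table 1 lists interventions and assessments under different headings.
- Baseline tests come before randomisation, so an injury there cannot result from an intervention not yet assigned.
- Usual care has no exercise intervention, so an injury to a usual-care participant in a 3RM test is not naturally described as related to one.

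**2. What other records could show a test injury?** Feasibility and safety measures lists the "3RM testing rate (with reasons for not completing the test"), together with reasons for refusal, reasons for drop-out, and HLST dose modifications. The stopping criteria add: "An injury related or unrelated to the exercise intervention will result in program modifications".

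**3. Putting the two together for an injury during a test:**

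| Where it happens | Within the Table 3 wording? | Other routes by which it could surface |
|---|---|---|
| Baseline, later HLST | No: precedes the intervention | Non-completion, refusal, drop-out, dose modification |
| Baseline, later usual care | No: precedes allocation, and no intervention follows | Non-completion at baseline (or at 12 weeks if the injury lasts), refusal, drop-out |
| 12 weeks, usual care | No: no intervention received | Non-completion of that test |
| 12 weeks, HLST | Depends on whether assessors attribute it to the training | Non-completion of that test |

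The routes in the last column record reasons or actions. None of them is a count of injuries, and none operates when the test is completed and the injury leads to no refusal, drop-out or programme change.

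**4. Does the gap reach the safety threshold?** No. The threshold concerns HLST participants with events likely related to the exercise intervention. With 48 randomised 1:1 there are 24 in HLST. Ten per cent of 24 is 2.4, so the threshold is passed at 3 participants (3/24 = 12.5%). Events from testing do not enter that numerator, and usual care does not enter the denominator.

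**The case against.** The strongest reply is that this is a condensed article. Adverse-event definitions, collection windows and forms usually sit in the full protocol and case report forms, which are not shown. Three places name adverse events without limit, Table 3 cells are short labels, and the Discussion sentence is a summary. A reader could also regard the tests as part of the exercise intervention in a broad sense; the sentence pairing testing with sessions does stand in the Intervention section. This part of the reply stands: wider recording is possible, and staff may do it. But the article does not leave the measure open. It states one, restricts it, and repeats the restriction, and no unrestricted mention supplies an alternative.

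It can also be said that harm from tests is already addressed. Discontinuation covers adverse events whether or not they are related to the intervention and mentions the physical assessments, and technique and pain are monitored during 3RM testing. This stands as protection for the individual. It does not produce a count.

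Three stronger readings are tempting, and the article does not support them:
- *That test injuries go unrecorded altogether.* Many would leave a trace through the routes listed above, including a lasting baseline injury that prevents the 12-week test.
- *That the number of test visits measures the problem.* The plan implies 48 baseline visits and, at the planned 38 evaluable, 48 + 38 = 86 in all. These are occasions for testing, not injuries, and the article gives no injury risk per test.
- *That a trial decision is compromised.* No threshold, efficacy analysis or stopping rule depends on this count.

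**Conclusion.** The point holds as a narrow one. As worded, Table 3 and the Discussion limit the adverse-event count to effects of the exercise intervention. An injury from a completed 3RM test, most clearly at baseline or in usual care, therefore need not be counted. This is a stated scope that is too narrow for a trial meant to establish feasibility and safety; it is not merely a missing detail.

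The effect is minor and its size cannot be derived from the article. The efficacy analysis, the >10% HLST threshold and individual protection are unaffected. The conclusion assumes that 3RM testing is not part of the exercise intervention, as the article's own wording suggests, and that no fuller document defines adverse events more widely. If one does, only the article's wording needs to be aligned with it. Confidence is medium, and the change is a cheap improvement, not a necessity.

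**What to change.** In Table 3, keep "injuries and/or undesired effects related to exercise intervention" and add the words *or to 3RM testing*, with the Discussion sentence brought into line. Count from the first baseline test in both arms, so that the baseline cell is also marked. Report testing-related events on a separate line, with everyone tested as the denominator. Leave the >10% HLST threshold as it is, since it is meant to judge the training.

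The cost is a wording change and slightly more recording by staff who already attend these visits. No extra visits or participants are needed. The downside is that more events may be reported; the separate line keeps them from being read as effects of the HLST programme.
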